#### **Sensitivity analysis:**

The primary analyses will be repeated replacing randomization arm by actual treatment to account for possible off-label use of and noncompliance to the investigational products.

#### **Subgroup analyses:**

All subgroup analyses will be pre-specified in the Statistical Analysis Plan. Any further subgroups will be considered ad hoc.

#### **Empirical Bayesian information borrowing method:**

In the case that a new experimental treatment is added into this platform trial, there will already be data collected from patients who are enrolled prior (past data). To incorporate the past control data with the concurrent control data from patients who are concurrently enrolled, empirical Bayesian information borrowing method will be used. Instead of using concurrent data only, combining past data with the concurrent data can potentially be advantageous in terms of statistical power and lower number of participants that are needed to be randomized to the control arm. This is particularly important for possible improved ethics and feasibility for the context of conducting a platform trial for SARS-CoV-2. Additionally, in the case that relevant external trial data become available, this empirical information borrowing method may be used. The DSMB, which will contain clinical experts, will make on whether to include or ignore the external trial data. The Study Statistician will assess the similarities of the external trial(s) to this clinical trial in terms of eligibility criteria, trial location, data collection procedures, and the reliability and comprehensiveness of the available dataset. If deemed appropriate, the empirical Bayesian information borrowing method will be used to determine the degree of the information that can be “borrowed” from the external dataset and be used for the statistical comparison.

As there are multiple randomized clinical trials that are either ongoing or being planned right now for SARS-CoV-2 with potentially relevant interventions, it is important to plan for an approach, such as this empirical Bayesian borrowing method, that can potentially incorporate these external data with the internal data. An important feature of this method is the avoidance of use of any subjective or informative prior distributions that may become a point of dispute in certain schools of thought.

|                                          |                 |
|------------------------------------------|-----------------|
| Date/version: May 19, 2020 – V1.0 | Page: 48 |
|------------------------------------------|-----------------|

The full technical details on the empirical Bayesian information borrowing method will be described in the Statistical Analysis Plan.

#### **Missing Data:**

Due to the design of the study and retention activities, we expect to be able measure outcomes on all participants. However, in the unlikely event of a missing test result, the missing data will be imputed.

#### **Interim Analysis:**

The DSMB will decide on a possible interim analysis during the trial after the sample size re-assessment based on the information on the observed recruitment rate, the CER, the drop-out rate, and the final sample size target, if applicable. The decision for interim analysis will be made in a blinded manner (e.g., based on pooled number of events). The interim monitoring plan (written by the Study Statistician) will define monitoring bounds to maintain the two-sided type I error rate at the desired 5% (e.g. 97.5% or higher probability of superiority over the control group). Should new experimental candidates be added during the trial, allocation ratios will be adapted to favor the new arms.

#### **12.3.2. Secondary endpoints**

All secondary endpoints will be assessed in the Intention-to-Treat population overall and by cohort.

##### **12.3.2.1. Safety Analyses**

All safety analyses will be performed on the Intention-to-Treat population. AEs will be compared by study group.

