| Patient Identification Card                                                                  |                                                  | X                                                   |                               |                              |                               |                              |                               |                               |                               |                               |                                                        |

1. Baseline visit may be performed at the same time as the screening visit. For patients without RT-PCR results, quick test for COVID-19 at the screening visit and randomization will be done after confirmation of SARS-CoV-2 infection. For patients with known RT-PCR positive results, screening and baseline visit will be done on the same day.
2. Visits made through telephone contact, calculated in relation to the randomization date. Home visits will be made for mid-nasal or saliva collection.

3. Only women of childbearing potential and / or potential to become pregnant. Urine pregnancy test for women with at least one menstruation in the last 12 months
4. After signing the Informed Consent Form.
5. Scales and questionnaires must be completed BEFORE any procedures of the proposed visit and must be self-applied. Only a person not related to the research can help the patient during the filling. In telephone visits, the patient must respond directly, at the time of contact.
6. Remind the patient that they will answer the questionnaire.
7. After completing the screening / baseline visit procedures and presenting all inclusion / exclusion criteria, patients should be immediately randomized.
8. The study medication will be administered as prescribed.
9. The first treatment dose under investigation must be administered on the same day of randomization (immediately after randomizing)
10. Maintain the administration of the product under investigation according to schedule. Patients administration to study drug as per protocol assessed. Discontinuation if adverse events prevent the medication from continuing.
11. Medication adherence will be assessed on Day 10 over the phone or in person.
12. As soon as the patient start the product under investigation.
13. Verification of clinical outcomes (e.g. symptoms, hospitalization and etc) will be done via telephone. On days when home visits are made, verifications of clinical outcomes may be done in person.

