| 
 
To test the efficacy of experimental interventions to prevent progression to LRTI, among persons with SARS-CoV-2 infection who are at high risk of progression
 
To test the efficacy of experimental interventions to reduce SARS-CoV-2 viral shedding
 
 | 
 
LRTI, defined by SpO2<93% or decline from baseline of 6% in 2 measurements at least 2 hours apart. Initially, the trial is statistically powered for this endpoint in high-risk population.
 
Proportion of persons with clearance of SARS-CoV-2 from nasal swabs or saliva, defined as 1 negative swab
 
 |
| 
 
To test the safety and adherence of experimental interventions for treatment of high-risk outpatients with SARS-CoV-2 infection
 
                                                                                                                                | 
 
Serious adverse events (including death, hospitalization) and adverse events resulting in treatment discontinuation up to 28 days
 
Proportion of non-adherent patients with interventions
 
                                                                                                                                   |
| 
 
To test whether any of the experimental interventions has an effect on hospitalization and mortality among persons who become hospitalized with COVID-19 disease (continued from primary outcome)
 
                                                              | 
 
Proportion hospitalized for COVID-19 progression
 
Days of hospitalization
 
Mortality for any causes after randomization up to 90 days
 
Mortality due to pulmonary complications
 
Mortality due to cardiovascular complications
 
                                                                      |

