## 12.2. *Populations for Analyses*

For analysis purposes, the following populations are defined and will be described in greater detail in the trial Statistical Analysis Plan:

| Population               | Description                                                                                                                                                                                |
|--------------------------|--------------------------------------------------------------------------------------------------------------------------------------------------------------------------------------------|
| Intention to Treat (ITT) | All enrolled participants who are randomized into the study: high-risk group for the primary clinical endpoint; high- and low-risk groups (separately) for the primary virologic endpoint. |
| Safety population        | All subjects who received at least 1 dose of study medication                                                                                                                              |
| PK evaluable             | Participants from the DBS Sub-study with at least 1 interpretable PK sample                                                                                                                |

DBS: dried blood spot; PK: pharmacokinetic;

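### The protocol defines a Safety population that no analysis uses, and assigns every safety analysis to ITT; the likely effect is small, but the sections conflict

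*Protocol*

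**What the plan says.** Section 12.2 of the protocol lists three populations for analysis. ITT is "All enrolled participants who are randomized into the study", whether or not they took anything. The Safety population is "All subjects who received at least 1 dose of study medication". The third is for pharmacokinetics.

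Section 12.3.2.1 then states "All safety analyses will be performed on the Intention-to-Treat population" and adds that adverse events are compared by study group. It does not say whether that means the assigned or the received treatment.

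Section 12.3.2 says "All secondary endpoints will be assessed in the Intention-to-Treat population overall and by cohort". This covers safety too, because Section 4.1 lists the safety endpoint among the secondary ones: "Serious adverse events (including death, hospitalization) and adverse events resulting in treatment discontinuation up to 28 days".

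The Safety population is not mentioned again. The one analysis by treatment received is the sensitivity analysis in Section 12.3.1: "The primary analyses will be repeated replacing randomization arm by actual treatment", planned "to account for possible off-label use of and noncompliance to the investigational products". It repeats the primary efficacy analyses and does not extend to adverse events.

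**The concern.** A population defined for analysis and then used by none means that one of the two sections does not say what was intended. The choice matters more for harms than for efficacy. Under ITT, a participant who never took a drug stays in that drug's adverse-event denominator, and one who took another arm's drug is counted under the wrong one. Never-dosed participants pull the comparison towards no difference. For efficacy that is cautious; for harms it favours the drug. Section 7.2.1 acknowledges that the regimens may prolong QT, so a fair estimate of the excess among those exposed is of real interest. Efficacy has a check by treatment received and adverse events have none.

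**Working it through.** **Text check.** Set side by side:

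| Section | Population named | Applies to |
|---|---|---|
| 12.2 | Safety (at least one dose) | no analysis named |
| 12.3.2 | ITT | all secondary endpoints, hence the safety endpoints of 4.1 |
| 12.3.2.1 | ITT | all safety analyses |
| 12.3.1, sensitivity | by actual treatment | primary analyses only |

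The conflict is confirmed from the text alone.

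**Size.** The protocol states no never-dosed share and no expected adverse-event rates, so there is no figure to reproduce. The inputs below are assumptions, except the 492 per arm (Section 5.1).

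Let d be the share never dosed in each arm, pt the event rate in those dosed with active drug, and pc the control rate, which is also taken as the rate in the never-dosed.

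- ITT rate on active = (1 − d) × pt + d × pc
- ITT risk difference = (1 − d) × (pt − pc)

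The relative shrinkage of the risk difference is therefore d itself.

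With pt = 20% and pc = 10% (true difference 10 points):

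- d = 1%: 0.99 × 20 + 0.01 × 10 = 19.9%, difference 9.9 points
- d = 5%: 0.95 × 20 + 0.05 × 10 = 19.5%, difference 9.5 points
- d = 10%: 0.90 × 20 + 0.10 × 10 = 19.0%, difference 9.0 points

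With pt = 10% and pc = 5% (true difference 5 points, risk ratio 2.00), two-sided 5% level, 492 per arm for ITT and 492 × (1 − d) per arm for the Safety population:

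| d | ITT difference | ITT risk ratio | Power, ITT | Power, Safety population |
|---|---|---|---|---|
| 0% | 5.00 | 2.00 | 84.7% | 84.7% |
| 1% | 4.95 | 1.99 | 84.1% | 84.3% |
| 5% | 4.75 | 1.95 | 81.4% | 82.8% |
| 10% | 4.50 | 1.90 | 77.8% | 80.8% |
| 20% | 4.00 | 1.80 | 69.2% | 76.0% |

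**Sensitivity to the assumption on the never-dosed.** If no adverse events are recorded in them and d is equal across arms, the risk difference still shrinks by d but the risk ratio stays at 2.00. If the shares differ, the ratio moves too. For 20% against 10%, with 10% never dosed on active and 2% on control: (0.90 × 20) / (0.98 × 10) = 18.0 / 9.8 = 1.84 instead of 2.00.

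**Plausible d.** Section 2.1, footnote 9, requires the first dose on the day of randomization, immediately afterwards. Section 10.1.1 puts randomization after PCR confirmation, with delivery and intake also on Day 0. Section 10.1.6 puts intake on Day 1, which may be the same day. This points to the upper rows of the table.

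**The case against.** The strongest reply has four parts.

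*The numbers are tiny.* At an assumed 1% never dosed, a 20% rate reads 19.9% and power changes by 0.2 points; at zero, the two populations are identical. This stands. A reader might infer that the plan materially hides drug harms. The documents do not support that: they give no never-dosed share, and the dosing rules point to a low one.

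*Noncompliance is only foreseen as possible.* A reader might also infer that cross-arm or off-label use makes the bias large. Section 12.3.1 calls such use possible, no figure for it is given or derivable, and Section 6.1.2 (items 12 and 16) excludes people already on hydroxychloroquine or protease inhibitors. Someone who stops after one dose belongs to both populations, so the choice between them changes nothing for that person. This also stands.

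*ITT is defensible for some safety events.* The safety endpoint includes death and hospitalization, which may be driven by the disease and overlap with the primary outcome. Section 7.5 says full blinding of patients and clinicians is not feasible, so refusing a first dose or seeking another drug could depend on arm and prognosis. Grouping these events by treatment received gives up the randomized comparison and can bias either way. It would therefore be too strong to conclude that ITT should be dropped for every safety analysis.

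*The SAP may settle it.* Sections 12.2 and 12.3 leave the detail of populations to the SAP, which was not available here. This part does not stand. Section 12.3.2.1 is a positive rule covering all safety analyses, so a SAP using the Safety population would contradict the protocol, and one following the protocol would leave the defined population idle.

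**Conclusion.** The conflict is certain: a Safety population is defined, two sections send safety to ITT, and no analysis uses the defined population. The direction of the bias from never-dosed participants is also clear, towards no difference, when their event rate is at or near background. Its size is a proportional shrinkage of the risk difference equal to the never-dosed share. Any number for that share is assumed, and the same-day dosing rule suggests it is small. The part due to wrong-arm or off-label exposure is not quantified. The change is worth making because it costs almost nothing and fixes the denominator for harms before data are seen, not because a large distortion has been shown.

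**What to change.** 1. In Section 12.3.2.1, state that adverse-event analyses use the Safety population of Section 12.2, with participants grouped by treatment actually received.
2. Add a rule for grouping anyone exposed to more than one study drug. It should also keep such participants distinct from those randomized to the combined arm that Section 5.1.1 foresees.
3. In Section 12.3.2, add the matching exception. If only Section 12.3.2.1 changes, Section 12.3.2 still sends the same endpoints to ITT and a new conflict replaces the old one.
4. Keep the ITT comparison of safety by randomized arm, in particular for death and hospitalization.
5. Report the number never dosed in each arm, so that the reader can see how far the two populations differ.

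The cost is a few sentences in two sections, carried into the SAP. No new data collection should be needed: adherence (Sections 2.1 and 10.1.2) and other medication taken (Section 7.8) are already recorded.

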##### **12.3.2.2. Hospitalization**

Hospitalization rates between the groups will be compared using logistic regression stratified by site. Number of days hospitalized will be described graphically and by median and interquartile range.

##### **12.3.2.3. Symptom Resolution**

Days with fever after randomization, respiratory symptoms (ordinal outcome) after randomization after randomization will be modeled using proportional odds regression method stratified by site.

The procedure assumes multinomial distributions for the marginal (i.e., time-specific) univariate ordinal responses and uses a working correlation structure to account for within-subject association between the repeated measures. Time-dependent covariates (e.g. ordinal responses at previous timepoints) will be included the statistical model.

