## Design:

This is an international multi-center adaptive randomized platform trial for the treatment of SARS-CoV-2 infection in high-risk adults not requiring hospital admission. In Brazil, stratified randomization will be done based on time since symptom onset (<120 hours vs. ≥120 hours) and age (<50 years vs ≥50 years).

Other chloroquine-based therapies, antiviral therapies, and other affordable candidate drug regimens that can be repurposed for COVID-19 may also be considered for this trial. The decision to add new therapeutic strategies will be made based on external findings with consultations of the local stakeholders. Therapies that can be repurposed for COVID-19 (e.g. lopinavir-ritonavir) will be prioritized since they offer more affordable and scalable therapeutic options for LMICs. The added arm may be tested with standardized eligibility criteria, outcomes, and measurements, as the other experimental interventions.

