| 
 
To test whether any of the experimental interventions is associated with decreased viral shedding from self-collected nasal swabs over 14 days: Day 1, Day 10 and Day 14 (+/-1 days)
 
 | 
 
Proportion of days with SARS-CoV-2 detected from mid-nasal swabs by PCR
 
Change in viral load on day 10 and day 14 after randomization from baseline
 
                                                                                                                                                                                                                                                                                                                                                                                                                                                                                                                                             |
| 
 
To test the quality-of-life (QoL) of experimental interventions for treatment of high-risk outpatients with SARS-CoV-2 infection
 
                                                     | 
 
Change in quality of life measured by Eq-5D-5L from baseline
 
                                                                                                                                                                                                                                                                                                                                                                                                                                                                                                                                                                                                                                             |

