### 7.4. ***Method of Treatment Assignment***

Participants will be randomized at an equal allocation ratio between experimental intervention and control groups at the level of the individual.

|                                          |                 |
|------------------------------------------|-----------------|
| Date/version: May 19, 2020 – V1.0 | Page: 30 |
|------------------------------------------|-----------------|

| Harmonized protocol document                                                          |
|---------------------------------------------------------------------------------------|
| Short title: Outpatient Management of SARS-CoV-2 for High-Risk Adults in LMICs |

The randomization plan will be overseen by the Study Statistician. The randomization code and resulting allocation list will be generated and overseen by the Study Statistician. The list will be blocked and stratified by site and risk level.

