#### **Primary analyses:**

The primary analyses will be conducted on the ITT population overall and by cohort. Participants randomized to each active arm will be compared to participants randomized to placebo (ascorbic acid). The primary analysis will make use of all participants randomized to placebo, whether contemporaneously enrolled or not using an Empirical Bayesian information borrowing method (described below). Due to anticipated heterogeneity in risk of disease progression, pre-specified baseline variables, including age, weight, and days of symptoms at time of enrollment will be included in the model to increase precision.

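### The symptom-resolution model in Section 12.3.2.3 names no baseline term for days since symptom onset or age, although the primary model adjusts for both

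*Protocol*

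**What the plan says.** **Symptom resolution (Protocol 12.3.2.3).** Days with fever and respiratory symptoms "will be modeled using proportional odds regression method stratified by site". The section describes a repeated-measures model with a working correlation structure and continues: "Time-dependent covariates (e.g. ordinal responses at previous timepoints) will be included the statistical model". It names neither days since onset nor age.

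**Primary model (Protocol 12.3.1, Primary analyses).** Because risk of progression is expected to vary between participants, "pre-specified baseline variables, including age, weight, and days of symptoms at time of enrollment will be included in the model to increase precision".

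**Randomisation strata.** The Synopsis (Design) says that in Brazil "stratified randomization will be done based on time since symptom onset", cut at 120 hours, and on age, cut at 50 years. Section 7.4 says instead: "The list will be blocked and stratified by site and risk level".

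**Hospitalization (Protocol 12.3.2.2).** "Hospitalization rates between the groups will be compared using logistic regression stratified by site". No other covariate is named there.

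**The concern.** The protocol treats days of symptoms and age as prognostic for the primary analysis, and the Synopsis also makes them strata. For the endpoints that count symptom days after randomisation it then describes a specific model in which neither appears. Version 3 limits entry to less than 8 days from onset, with onset as day 0, so participants can enter anywhere from day 0 to day 7 of illness. It is plausible that the symptom days still to come depend on that.

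In a logit-type model, omitting a prognostic baseline variable pulls the estimated treatment odds ratio towards 1 and lowers power. If the omitted variable was also a randomisation stratum, ignoring it usually makes the test somewhat conservative. What is at stake is efficiency on secondary endpoints. Validity under the null is not in question.

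**Working it through.** **1. Stated figure.** The protocol gives no power or sample size for the symptom endpoints, so there is nothing to reproduce. The planned sizes of 492 per arm (Synopsis, 5.1, 12.1) and 165 per arm (3, 5.2, 12.1) serve below only as arm sizes. Whether 492 supports its own hospitalization claim is a separate question, and nothing here depends on it.

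**2. The sections side by side.**

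| Section | Days since onset | Age | Site | Other terms named |
|---|---|---|---|---|
| Synopsis, Design (strata) | yes | yes | no | none |
| 7.4 (strata) | no | no | yes | risk level |
| 12.3.1 (primary model) | yes | yes | no | weight |
| 12.3.2.2 (hospitalization) | no | no | yes | none |
| 12.3.2.3 (symptoms) | no | no | yes | time-dependent covariates, e.g. earlier ordinal responses |

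The site term in 12.3.2.2 and 12.3.2.3 partly matches Section 7.4 but neither Synopsis stratum. The mismatch with Section 12.3.1 stands whichever statement of the strata is right.

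**3. Size, by simulation under assumptions.** The documents give no association between illness day or age and symptom outcomes, so a range was used.

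- Outcome: five ordered categories at one time point. Latent value = ln(OR treatment) × arm + ln(OR onset) × onset + ln(OR age) × age + logistic error, cut at −1.4, −0.4, 0.4 and 1.4.
- Onset and age: independent binary factors, each split evenly.
- Treatment OR: 1.38 with 492 per arm and 1.72 with 165 per arm, chosen to give roughly 80% power when neither factor is prognostic.
- Test: cumulative logit, |z| > 1.96, fitted to the same data sets with arm alone and with arm, onset and age.
- 1,500 replicates per row, so the standard error of a power near 80% is √(0.8 × 0.2 / 1500) ≈ 0.010, about 1 point.

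| Per arm | OR onset / OR age | Power without | Power with | Gain (points) |
|---|---|---|---|---|
| 492 | 1 / 1 | 81.8% | 81.8% | 0.0 |
| 492 | 1.5 / 1.25 | 80.2% | 81.1% | 0.9 |
| 492 | 2 / 1.5 | 79.1% | 82.5% | 3.3 |
| 492 | 3 / 2 | 73.4% | 79.9% | 6.5 |
| 492 | 5 / 2 | 68.4% | 80.1% | 11.7 |
| 165 | 1 / 1 | 78.7% | 78.5% | −0.1 |
| 165 | 1.5 / 1.25 | 78.9% | 78.1% | −0.8 |
| 165 | 2 / 1.5 | 77.5% | 80.6% | 3.1 |
| 165 | 3 / 2 | 70.9% | 76.7% | 5.8 |
| 165 | 5 / 2 | 66.1% | 76.7% | 10.6 |

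Gains were taken before rounding. The small negative values are within simulation error.

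**4. Limits.** Site strata, repeated measures and earlier responses were not simulated. The table shows what the baseline terms are worth in a model without earlier responses. In the planned model, earlier responses may already carry part of that information.

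**The case against.** The best counter-argument is that Section 12.3 calls itself a brief summary and leaves detailed analysis to the SAP, where covariates could be added. Section 12.3.2.3 also does not rule out further baseline terms. That limits the weight of the point but does not remove it. The section goes beyond naming an endpoint: it states the model, the stratifier, the correlation handling and a type of covariate, and these do not match the primary model. Aligning them corrects stated text.

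A second argument is that earlier ordinal responses already adjust for prognosis. They may do so in part, and if day 0 counts as an earlier timepoint, some baseline severity enters too. But responses after randomisation are affected by treatment. Conditioning on them can absorb part of the treatment effect, so they do not replace baseline covariates.

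A third argument is that odds ratios are non-collapsible: adding covariates changes the quantity estimated, in a model described as marginal. This is correct and is the one real cost of the change.

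A reader might also infer more than the documents support:

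- **That site is the only term in the symptom model.** It is not; time-dependent covariates are named.
- **That the trial certainly randomises by onset and age.** Only the Synopsis says so, and Section 7.4 says otherwise.
- **That these endpoints depend more on illness day than any others, so the loss must be large.** No figure supports this. If the chance of recovery were the same on every day of illness, days since onset would not predict the days remaining.
- **That EQ-5D-5L, viral load and WURSS-11 will be analysed as raw change scores.** Section 4.1 only defines these endpoints. No section states their analysis, and a change endpoint is compatible with adjustment for baseline.

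**Conclusion.** The point holds as one of efficiency and consistency on secondary endpoints. The symptom model names neither days since onset nor age, while the primary model uses both to gain precision. The missing terms do not bias the comparison.

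The possible gain in power is about 0 to 3 points if the two factors are weak to moderate (odds ratios up to 2), and about 6 to 12 points if onset is strong (odds ratio 3 to 5, with age at 2). These figures rest on assumed prognostic strengths, evenly split binary factors and a single time point, and could be smaller once earlier responses are in the model. Because the gain may be negligible, the case for the change rests mainly on its very low cost and on removing an inconsistency. The conflict between the Synopsis and Section 7.4 needs settling in any event, because until then the matching strata cannot be named.

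**What to change.** 1. Reconcile the Synopsis (Design) with Section 7.4, so that one list of randomisation strata applies throughout.
2. In Section 12.3.2.3, add as baseline terms the actual stratification factors, continuous days since onset, continuous age and baseline symptom severity. State that adjustment for prognosis rests on these terms and not on responses after randomisation.
3. Apply the same check to Section 12.3.2.2. Hospitalization is also part of the primary endpoint in Section 4.1, so a site-only model there sits beside an adjusted primary model.
4. State that the reported odds ratio is conditional on the listed covariates.

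**Cost.** A few sentences. Time of onset is needed for eligibility and for the Synopsis strata, and the schedule in Section 2.1 collects demography at screening and WURSS-11 at baseline, so no new data or visits are required. The downside is that the adjusted odds ratio differs from the unadjusted one and must be interpreted as conditional.
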